### Data management

All participant consent forms and quantitative study data will be stored at UCL. Consent forms identifying participants will be stored separately from case report forms, which will not bear the participant’s name or other personal identifiable data. All paper forms will be kept in locked cabinets in secure offices. Study researchers will develop and manage a secure database for all quantitative study data using SPSS software [55] on the secure IT network at University College London. Qualitative audio files and transcripts will be kept similarly securely at McPin offices for the duration of the study. Anonymised electronic copies of qualitative transcripts will be stored using QSR International’s NVivo 10 qualitative data analysis software [56] at the McPin Foundation. After the study, all data will be archived securely at UCL.

### Data monitoring

The study sponsors, University College London, act as guarantors for the trial, including insurance and indemnity arrangements, and are responsible for overseeing and auditing trial conduct, through the UCL/UCLH Joint Research Office. Any proposed changes to the trial protocol during the study will be agreed by the study team and submitted for approval to the research ethics committee. Protocol modifications will then be communicated to the sponsor, site principle investigators, participating NHS trusts and trial participants via email or telephone. Service users, staff and other stakeholders providing data for the trial will all provide informed consent to take part, using ethically approved procedures.

The trial will be run day-to-day by a study management group including the Chief Investigators and other senior academics and clinicians. The study management group will meet approximately six times per year and will send updates to a Principal Investigator at each site. Independent advice to the study management group and oversight of the study is provided by a trial steering committee, which is independent of the sponsor and will meet at least annually during the trial. The steering committee comprises senior academics, a statistician, and a service user representative. A data monitoring committee (DMC) is not planned for this small feasibility trial, but the trial steering committee will advise if any role for a separate DMC is indicated during the trial. No interim analyses are planned, and no stopping criteria are pre-set.

The study researcher will screen for serious adverse events through review of intervention session logs, monthly updates from the clinical supervisors, and review of patient records by clinicians in participating services. Any serious adverse events reported to the study team will be reviewed by the study Chief Investigator and by the chair of the trial steering committee as an independent reviewer. Any adverse events assessed as study-related will be reported, with the trial steering committee chair’s recommendation, to the study sponsor.

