## Methods

### Design

The study is a feasibility trial with block randomisation conducted in two sites in London (United Kingdom). Randomisation will be stratified by site with an allocation ratio of 3:1, intervention to control. The trial compares Community Navigation, a co-produced, newly developed social intervention provided in addition to standard care from secondary mental health services, to a control group receiving standard care and written information about local community resources.

The design as described here adheres to the Standard Protocol Items: Recommendations for Interventional Trials (SPIRIT) guidelines [26], including a flow diagram (Fig. 1) and a SPIRIT schedule (Table 1). A copy of the SPIRIT Checklist, detailing where each recommended element of the protocol is included in this paper, is provided as Additional file 1.

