##### Supervision

Regular group supervision (monthly at each of the two services in this trial) will provide support with delivering the study activities and address issues or challenges in working with specific participants. Supervisors are mental health practitioners from participating services who know the study participants, bring clinical expertise and local service knowledge, and who are familiar with and supportive of the structure and aims of the Community Navigator programme. The Community Navigators will also have immediate access at all times to clinical staff in the event of any immediate concerns about participants’ safety or wellbeing.

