We will seek information from Trust Informatics teams regarding participants’ current diagnosis, care cluster, attended and missed face-to-face appointments with their mental health team, use of other community mental health services, admission to acute care, days in inpatient care, and use of the Mental Health Act. These records will be sought for the six months prior to baseline and at six months’ follow-up for the intervention period. Participants’ use of social care services will also be sought from local council social care records at the same time points.

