#### Process recording

To facilitate examination of the intervention content, Community Navigators will complete session logs following each session with a participant, detailing the location of the meeting and its content (selecting from a list of planned types of support). Feedback will be sought from intervention-arm participants for two of their Community Navigation sessions. Participants will be contacted as soon as possible (ideally within 3 days) following a randomly selected session and asked questions over the phone by a study researcher. Questions, taken from a standard feedback form, will cover the location of the meeting, what types of support were provided (with the same options as in Community Navigators’ session logs), and a rating of how they found the session on a five-point scale (from very good to very poor). The aim is to have data spanning all ten sessions without having to ask participants for feedback after each session.

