### Data analysis

Factors relating to the acceptability of the intervention and the feasibility of trial procedures, and completion rates for potential primary and secondary outcomes in a definitive RCT will be reported.

Feasibility will be assessed by:Recruitment duration; the time period from recruitment of the first trial participant to meeting the trial recruitment target (40 participants).Recruitment; the number of participants screened, the number of those screened who are eligible, and the number of eligible participants who consent to participate in the study by four months.Attrition; the number of participants who consent to participate that remain in the study until the end of follow up at six months.Intervention take-up rate for those in the intervention arm: the proportion of participants who met their Community NavigatorImplementation of the intervention: the proportion of participants that maintained engagement with a Community Navigator and the number of sessions of support provided. A minimum threshold of at least three meetings with a Community Navigator has been set to represent treatment as per protocol.Number of adverse events recorded in each study arm until the end of follow up at six months.

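### By-arm adverse event counts are open to unequal detection, and the plan counts all adverse events while describing a search for serious ones only

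*Protocol article*

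**What the plan says.** Among its feasibility measures, the Data analysis section of the protocol article lists the "Number of adverse events recorded in each study arm until the end of follow up at six months". It sets no severity limit.

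The Data monitoring section says how events are found: "The study researcher will screen for serious adverse events through review of intervention session logs, monthly updates from the clinical supervisors", and the same sentence ends "and review of patient records by clinicians in participating services". That makes three routes, all described for serious events.

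Other sections show whom each route can reach:

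- Process recording (under Outcome measures): "Community Navigators will complete session logs following each session with a participant".
- Supervision: the monthly group sessions for Navigators "will provide support with delivering the study activities and address issues or challenges in working with specific participants". The same section adds: "Supervisors are mental health practitioners from participating services who know the study participants".
- Measures: Trust Informatics teams will be asked, without restriction by arm, for data that include "admission to acute care, days in inpatient care, and use of the Mental Health Act".
- Design: "Randomisation will be stratified by site with an allocation ratio of 3:1, intervention to control", which gives 30 and 10 participants.

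**The concern.** Two things do not fit together.

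First, the count is set out by arm, but the arms are not watched equally. An event in an intervention participant can surface through a log, a supervisor or the records. The only route clearly stated to reach a control participant is the records. If some events escape the records, the intervention arm will show more of them per person even when the true risk is the same.

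Second, the scope differs between sections. One counts adverse events and the other looks for serious ones. No systematic route is described for non-serious events, so a count that includes them would depend on what happened to be mentioned, and Navigator contact gives more occasions for that in one arm.

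What is at stake is how the safety line of the feasibility report is read, and whether the same procedure is carried into the definitive trial that this study is meant to inform. A larger trial would reduce chance variation but would not remove unequal detection.

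**Working it through.** **Coverage of each route**

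| Route (Data monitoring) | Intervention, n = 30 | Control, n = 10 |
|---|---|---|
| Session logs | Yes | None possible, as there are no sessions |
| Supervisor updates | Yes, through Navigator supervision | Not stated; supervisors may know of events, but no duty to report on controls is given |
| Clinician records review | Yes | Yes; no limit by arm is stated, and all participants are on a service caseload at entry |

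**Size of the possible distortion**

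The article gives no event rate and no detection rate, so there is no figure of its own to reproduce. The allocation arithmetic agrees: 40 × 3/4 = 30 and 40 × 1/4 = 10.

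Assumptions, none of them from the documents:

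- the true per-person risk is equal in the two arms;
- the records review finds a share *s* of events in either arm;
- logs and supervisors together find a share *a* of events, independently of the records and in the intervention arm only.

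The per-person ratio of recorded events is then

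R = [1 − (1 − s)(1 − a)] / s,

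and the raw count ratio is 3R because of the 3:1 allocation. For example, with s = 0.90 and a = 0.70, R = (1 − 0.10 × 0.30)/0.90 = 0.97/0.90 = 1.08.

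| s | R at a = 0.30 | R at a = 0.70 | Raw count ratio |
|---|---|---|---|
| 1.00 | 1.00 | 1.00 | 3.00 |
| 0.95 | 1.02 | 1.04 | 3.05 to 3.11 |
| 0.90 | 1.03 | 1.08 | 3.10 to 3.23 |
| 0.70 | 1.13 | 1.30 | 3.39 to 3.90 |
| 0.50 | 1.30 | 1.70 | 3.90 to 5.10 |

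Hospital admissions are likely to be recorded, which points to the upper rows. Events that do not readily reach the records belong in the lower rows. If supervisors also report on controls, R falls.

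If only sources common to both arms are used (a = 0), R = 1.00 at any *s*. The raw count ratio is still 3.00, which is why denominators are needed.

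**Chance, for scale**

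At an assumed 10% risk, the probability that no participant has an event is 0.9^10 = 0.35 among 10 controls and 0.9^30 = 0.04 among 30 intervention participants. Zero events in 10 leaves a one-sided 95% upper limit of 1 − 0.05^(1/10) = 0.26.

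**The case against.** A reader might infer that the trial plans a safety comparison that is biased by design, with events sought only where the intervention is delivered. The documents do not support that.

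- The records review is in the same sentence as the other two routes and is not limited to one arm.
- Supervisors know the study participants, so their coverage of controls is unstated, not shown to be absent.
- The count is one descriptive feasibility measure. No test, threshold or progression rule uses it, no stopping criteria are set, and serious events are reviewed case by case with independent input. For that review, extra detection in the exposed arm is an advantage.
- The threefold excess in raw counts is not bias. The denominators are stated, and anyone can divide by them.
- With 10 controls, chance outweighs a distortion of a few per cent, so equal ascertainment would not make the arms informatively comparable.
- The scope mismatch may be shorthand. Data monitoring itself drops the word serious when it turns to study-related events, and a condensed article may have lost the distinction.

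Most of this stands, and it limits the point. Two things remain. Tabulating a count for each arm invites a side-by-side reading, and the article's caution about small size does not cover systematic differences in detection. And as written, the two sections describe different sets of events.

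**Conclusion.** The point holds in a limited form. Of the three routes, one exists only in the intervention arm, one arises mainly from work with that arm, and one clearly covers both. The by-arm counts are therefore open to differential ascertainment, and the reported scope is wider than the surveillance described.

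The size is unknown. Under equal true risk and the assumptions above, the per-person ratio is 1.00 with complete records and about 1.02 to 1.08 at 90 to 95% completeness. It reaches 1.30 to 1.70 only if the records miss half of the events. It would go too far to say that a real harm signal could not be told apart from detection: the admission and Mental Health Act data already sought offer a check on several events likely to be serious, in both arms alike.

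Severity is minor to moderate, because this is a 40-person feasibility trial with no formal safety comparison.

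**What to change.** 1. Base the by-arm figure on sources applied identically to all 40 participants: the planned clinician records review, supported by the Trust Informatics data on admissions, inpatient days and Mental Health Act use.
2. List events found only through session logs or supervisor updates separately, with the source of each event shown. They still go to case review as now.
3. Report participants with at least one event over the number randomised in each arm, since allocation is 3:1.
4. Reconcile Data analysis with Data monitoring: either limit the reported measure to serious adverse events, or describe how non-serious events are found in both arms.

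The cost is mainly wording and a source field on the event record, with no new data source unless the trial chooses to search for non-serious events. The downside is that the by-arm figure rests on fewer sources and may miss events known from the logs; the separate list keeps those visible. One limit remains: Navigators have direct access to clinical staff and refer participants back to the clinical team, so their contact may lead some intervention-arm events to be recorded that would go unrecorded in a control. The report should say so.

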## Discussion

### Strengths and limitations

This intervention is being developed by a working group of 12 people including experts by experience, practitioners and members of the research team. Service users and clinicians from the mental health teams involved in the study, as well as experts delivering similar programmes, are being consulted. This increases the likelihood that this intervention is relevant to the study population and works within these clinical settings [57]. The literature also suggests that coproduction makes sustainable change and translation of knowledge into practice more likely [58, 59].

Throughout this study, Medical Research Council guidance on developing and evaluating complex interventions [25] is being followed in a robust manner. Before starting this feasibility trial, Community Navigation was piloted with ten service users to test and refine the intervention and procedures for recruitment and outcomes data collection, enhancing their acceptability to participants, clinicians and researchers. Additionally, preliminary testing allowed us to provide further training for the Community Navigators and support consistent delivery of the intervention.

The use of qualitative interviews with service users, their friends and family, clinicians, and Community Navigators will inform us about people’s experiences. This will help establish the acceptability and feasibility of the programme, and inform any further refinements to the intervention needed before a future definitive trial. The interviews will also be used to refine a Theory of Change, modelling the resources needed to deliver the intervention, its content and the outcomes achieved. Qualitative interviews will provide insight into people’s experiences, which may reveal the mechanisms through which the support has its effect, and what factors need to be in place to achieve successful outcomes.

This feasibility trial will run across two NHS sites including affluent areas and areas of high deprivation as well as ethnically diverse populations. Due to limitations in resources, we are only able to include service users who can communicate in English. This limits the generalizability of our findings to English-speakers within these services. However, this is still a diverse group of service users. Except for this requirement, we have kept the inclusion and exclusion criteria broad so that most users of the participating services will be eligible to take part. This will maximise learning about the extent to which Community Navigation is generally feasible and acceptable in addition to standard care from secondary mental health services.

As researchers will have ongoing contact with clinical teams, Community Navigators and participants throughout the intervention, it will not be possible for researchers to be blinded during outcomes data collection. However, outcome measures will be self-administered so should not be influenced by researcher bias. In a future definitive RCT, with more resources available, it would be possible for researchers to be blinded, but this procedure will not be tested in this trial.

This intervention takes one approach to targeting loneliness. There are other components of loneliness which we are not attempting to tackle. For example, people who feel lonely may have cognitive biases, such as negative evaluations of others, and a lack of interpersonal trust [60]. Alternative interventions for loneliness try to change people’s cognitions about social relationships, for example cognitive ‘reframing’ of loneliness to increase perceived control over reducing it [61]. Community navigation does not include a cognitive component, or other approaches such as social skills training and wider community changes. With current evidence, it is unclear which approach to reducing loneliness and increasing people’s community connections may be most effective [19].

### Research implications

Although social interventions such as Community Navigation are advocated in policy, and have been reported positively, there is little evidence to date regarding their effectiveness [24]. The appropriateness of using such interventions (most commonly provided in primary care) for a population using specialist mental health services with enduring mental health problems and complex needs is also unclear from current research. In this feasibility trial, we attempt to address these issues and provide preliminary evidence of the acceptability of this support.

Evidence regarding the feasibility of Community Navigation should provide a basis for future research. If this feasibility trial of the Community Navigator programme yields promising results, it will provide a clearly defined structure and set of resources that can be definitively tested in a large-scale RCT. In addition, this study should reveal barriers and facilitators to implementing this social intervention within an RCT. This should enable us to implement the most effective recruitment strategy, develop clear trial procedures, consider key roles of clinical staff in the study, and address people’s willingness to participate in this type of intervention. Our findings may have broader implications to inform randomised trials of social interventions within mental health services and in other areas.

### Implications for policy and practice

Loneliness can negatively influence the physical, psychological and social wellbeing of individuals. Interventions which alleviate loneliness are beneficial in their own right and hold promise in improving people’s mental health, as well as having wider benefits for health outcomes and health service resources. If successful, this feasibility study will provide a clearly manualised social intervention designed to reduce loneliness, with evidence of acceptability and feasibility for use in mental health settings. As UK policy already advocates this kind of social intervention, and related programmes are already running, this would be immediately useful in guiding commissioning and delivery. It would provide a manualised intervention ready for delivery in clinical settings. This feasibility trial will also inform and support a future larger RCT of Community Navigation, which could establish the effectiveness of this type of support and potential cost savings, calculated through an economic analysis.

## Trial status

This is protocol version 2 (09/02/2017) which received ethical approval on 14/03/2017 and Health Research Authority approval on 23/03/17. Participant recruitment began on 24/04/2017, is ongoing at the time this paper was submitted, and is expected to be complete by the end of August 2017.

## Abbreviations

Barnet CCT: Barnet Complex Care Team
Camden and Islington CDAT Team: Camden and Islington Complex Depression Anxiety and Trauma Team
CIC: Community Interest Company
DMC: Data Monitoring and Ethics Committee
NIHR SSCR: National Institute for Health Research School for Social Care Research
RCT: Randomised Controlled Trial
SPIRIT: Standard Protocol Items: Recommendations for Interventional Trials
UCL: University College London
